#### Clinical management at first colposcopy

The clinical management of women attending colposcopy is defined by the enrolment cytology and the colposcopy results as shown in figure 2.

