**Methods and analysis:**

Women aged 30–64 years are screened with HPV testing and Pap across 12 study centres in Latin America. Screened positives have colposcopy with biopsy and treatment of lesions. Women with no evident disease are recalled 18 months later for another HPV test; those HPV-positive undergo colposcopy with biopsy and treatment as needed. Biological specimens are collected in different visits for triage testing, which is not used for clinical management. The study outcome is histological high-grade squamous intraepithelial or worse lesions (HSIL+) under the lower anogenital squamous terminology. About 50 000 women will be screened and 500 HSIL+ cases detected (at initial and 18 months screening). Performance measures (sensitivity, specificity and predictive values) of triage techniques to detect HSIL+ will be estimated and compared with adjustment by age and study centre.

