**Trial registration number:**

NCT01881659

Strengths and limitation of this studyThe study design in which additional samples from all women screened with HPV and cytology are collected at screening simulating a reflex-testing scheme whenever possible, will allow the evaluation of triage techniques without influencing the outcome of the study, as tests are performed or evaluated after disease confirmation.This is the largest cervical screening study in Latin America with more than 500 histologically confirmed high-grade squamous intraepithelial lesions (HSILs) expected that will permit evaluation of several triage tests, alone or in combination, for HPV-positive women.A large number of women are being screened with HPV testing in Latin America, where the majority of women would not otherwise benefit from high-quality cervical screening.The multicentric nature of the study will allow capturing experiences from areas which are geographically, culturally and socio-economically distinct from each other and with different health systems/areas that may face common challenges but that require different approaches in accordance with their context.Colposcopy and collection of biopsies was not performed in HPV-negative women (only in a subset who had abnormal cytology), potentially introducing verification bias when assessing absolute performance measures of screening tests to be used in primary screening; however, the study design will allow unbiased evaluation of triage tests.

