#### Cytology

Conventional cytology or Pap has been used since the 1950s in primary screening and has succeeded in decreasing cervical cancer in several HICs, particularly where women have had cytology frequently and high adherence to diagnosis and treatment has been achieved. This has not happened in LMIC, where usually coverage has been low and access to diagnosis and treatment has been limited.

Liquid-based cytology (LBC) uses the same principles and criteria of Pap and is replacing Pap in HICs because it offers the opportunity for reflex testing and significantly reduces the number of inadequate samples,^15^ although in terms of screening performance both are comparable.^16 17^ More recently, computer-scanned liquid-based slide algorithms showed promising results by improving detection of HPV-positive cervical intraepithelial neoplasia grade 3 (CIN3)/women with adenocarcinoma in situ (AIS).^18^

HPV testing followed by triage with cytology (Pap or LBC) is the immediate screening modality to be used in HPV-based screening settings with high cytology capacity. However, the limited sensitivity of cytology might detriment HPV testing sensitivity, especially in places where strict quality assurance cannot be ensured.

It has been postulated that prior knowledge of HPV status may improve the performance of cytology since the interpreter will be more meticulous when reading a smear of an HPV-positive woman. However, results from studies have not been fully consistent; some have shown increases in the proportion of abnormal results^19^ leading to increased CIN grade 2 or worse lesions (CIN2+) detection^20^ and potential reduction of immediate referrals to colposcopy,^21^ while at least one study reported losses in cytology accuracy with increases of false-positive readings and losses in specificity.^22^ We plan to evaluate the performance of cytology, both Pap and LBC, with and without prior knowledge of HPV status, as triage tests.

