##### Women with cytology HSIL or more severe lesion (HSIL+)

Treatment with LLETZ should be offered without prior histology confirmation to women with a ‘positive major’ colposcopy, whenever possible. Biopsies should be collected if the colposcopy is considered ‘positive minor’ or where LLETZ without confirmed CIN2 is not allowed. If a transformation zone type 3 (TZ3) is observed, an endocervical sample should be collected and an excision type 3 (LLETZ to excise lesions which endocervical extent is not visible) diagnostic or therapeutic should be performed.

The clinical management of women with discordant results: lesions less than CIN2 (<CIN2) or those with negative colposcopy but with HSIL+ cytology should be revised at multidisciplinary team (MDTs) meetings, that are attended by the cytologist, pathologist, colposcopist and the local principal investigator at least. During the MDT, cytology, histology and colposcopy results, considering the age and parity of the woman, should be discussed to finally recommend treatment or recall for a second HPV test 18 months later. In the benefit of women, who may be lost to follow-up, recommendation for LLETZ will be prioritised above 18 months recall.

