##### Women with cytology less than HSIL (<HSIL), unsatisfactory or unknown cytology

Biopsies should be collected from all women with positive colposcopy. An endocervical sample should be collected from women with TZ3 and if the result of this sample is HSIL+, treatment (excision type 2 or 3) should be offered. Women with histology <CIN2, negative colposcopy and those with a TZ3 and <HSIL on the endocervical sample should be recalled at 18 months. MDTs should be carried out when the colposcopy is positive major but the histology is <CIN2.

The colposcopic impression using a standard colposcopy nomenclature and specific colposcopy features (eg, size and location of observed lesions, number and severity of biopsies collected) are recorded in colposcopy study forms.

At the treatment visit, first a colposcopy is done followed by LLETZ. The reason and type of LLETZ as well as the colposcopic impression are recorded in treatment study forms. A pregnancy test is administered to participants before treatment with LLETZ and local consent forms for surgical procedures are sought. Self-reported adverse events are documented.

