A few limitations of the study design should be mentioned. First, capacity (personnel and facilities) differences among study centres could influence results. To prevent this, special attention is given to training health professionals involved in the study: clinicians collecting samples, colposcopists, pathologists, molecular biologists among others. The training includes good clinical practices, research governance and up-to-date specialty training to standardise procedures all over the study. Second, we are not performing colposcopy nor collecting biopsies in HPV-negative women, potentially introducing verification bias for evaluation of techniques in primary screening but not in triage. However, as cotesting with Pap is being done, and although the rate of cytological abnormalities among HPV-negative women will be usually low, we will have a small group of them having colposcopy helping us to estimate disease among HPV negatives. We also do not collect random biopsies at colposcopy when acetowhite lesions are not evident, thus, it is possible that some lesions are being missed. To minimise missing lesions, the study protocol includes: (1) 2–3 biopsies of any acetowhite areas observed are collected at colposcopy with ranking of severity of biopsies collected to further evaluate the use of multiple and severity of biopsy collection; and (2) a second round screening at 18 months for women with no evident disease at initial screening, providing an additional opportunity of detecting any missed disease at initial screening.

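### The claim of unbiased triage evaluation does not hold for cytology: the enrolment Pap is a triage candidate and, jointly with colposcopy, determines how disease is verified

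*Protocol article*

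**What the plan says.** Three statements describe triage evaluation as independent of management or free of verification bias:

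- The strengths and limitations box: "the study design will allow unbiased evaluation of triage tests".
- The Discussion, on not examining HPV-negative women: "potentially introducing verification bias for evaluation of techniques in primary screening but not in triage".
- The abstract: "Biological specimens are collected in different visits for triage testing, which is not used for clinical management".

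None of them excepts cytology. The section on cytology makes it a candidate: "We plan to evaluate the performance of cytology, both Pap and LBC, with and without prior knowledge of HPV status, as triage tests".

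The management sections give cytology a second role: "The clinical management of women attending colposcopy is defined by the enrolment cytology and the colposcopy results as shown in figure 2". Under HSIL+ cytology, "Treatment with LLETZ should be offered without prior histology confirmation to women with a" major positive colposcopy, where possible. A TZ3 leads to an excision. Discordant cases (negative colposcopy, or histology below CIN2) go to a multidisciplinary team (MDT), where "recommendation for LLETZ will be prioritised above 18 months recall". Under cytology below HSIL, the rule is: "Women with histology <CIN2, negative colposcopy and those with a TZ3 and <HSIL on the endocervical sample should be recalled at 18 months". An MDT is held in that group only when colposcopy is major and histology is below CIN2.

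**The concern.** A triage test is judged against histology, so the search for disease should not depend on that test's result. Here it does for one candidate. Among women with the same colposcopic finding, those with HSIL+ cytology are more likely to have a whole excised specimen examined. Any HSIL+ found only because of that extra tissue is Pap-positive at the HSIL cut-off by construction. An equivalent lesion in a woman with lower cytology may go unseen. Table 1 counts histology below the threshold, a negative 18-month HPV test and a final negative colposcopy as no disease. A missed lesion can therefore become a true negative for Pap and a false positive for a marker that detected it, so specificity and predictive values are exposed as well as sensitivity.

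Whether cytology is good enough as triage is one of the article's main questions (Introduction of the abstract, and Discussion). The sample size is built on a 5-point difference in sensitivity, so a shift of a few points matters.

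The design does protect another candidate. VIA results are kept out of management and are not discussed with other staff, except when cancer is suspected (Visual methods; Visit 2). Enrolment cytology has no such separation.

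**Working it through.** **Step 1. Same finding, two work-ups** (from the two management sections and Visit 2)

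| Finding at first colposcopy | HSIL+ cytology | Cytology below HSIL |
|---|---|---|
| TZ3 | Endocervical sample and excision | Endocervical sample; excision only if that is HSIL+ |
| Negative colposcopy | MDT favouring LLETZ | 18-month recall; no biopsy without an acetowhite area |
| Histology below CIN2, colposcopy not major | MDT favouring LLETZ | 18-month recall |
| Histology below CIN2, colposcopy major | MDT | MDT |
| Major colposcopy, first step | LLETZ without prior histology where possible | Biopsy |

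The first three rows show differential verification by cytology. In the last two, disease would mostly be found under either pathway.

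**Step 2. The plan's figures.** The article gives no figure for this bias. The usable yardsticks are 50 000 × 1% = 500 HSIL+ cases and the 5-point target difference. The stated power (80% at discordance up to 10%) looks conservative: with 500 cases and a two-sided 0.05 level, the paired formula gives 94.5% if discordance means the total. The supplementary calculation is not shown, and nothing below depends on the power.

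**Step 3. How large could it be?** Let s be true Pap sensitivity at the HSIL cut-off. Let r be the chance that a true HSIL+ is found over the whole study when cytology is below HSIL, divided by that chance when cytology is HSIL+. Then

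observed sensitivity = s / (s + (1 − s) r).

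Both s and r are assumptions. With s = 0.50:

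- r = 0.95: 0.50/0.975 = 51.3%, inflation 1.3 points
- r = 0.90: 0.50/0.95 = 52.6%, 2.6 points
- r = 0.80: 0.50/0.90 = 55.6%, 5.6 points
- r = 0.70: 0.50/0.85 = 58.8%, 8.8 points
- r = 1: none

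Inflation reaches 5 points at r = (0.50 × 0.45)/(0.50 × 0.55) = 0.82. For s from 0.3 to 0.7 that threshold lies between 0.78 and 0.82.

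**Step 4. The same in counts.** Assume 480 cases found whatever the cytology, Pap positive in 288 (60%) and a comparator in 312 (65%). Let k further cases be found only through cytology-driven excision, with the comparator positive in 65% of them. Pap sensitivity is (288 + k)/(480 + k):

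- k = 10: 298/490 = 60.8%, gap 4.2 points
- k = 20: 308/500 = 61.6%, gap 3.4 points
- k = 40: 328/520 = 63.1%, gap 1.9 points

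**Step 5. What reduces or opposes it**

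- *Correlated comparator.* With k = 40 and the comparator positive in 90% of the extra cases, it reaches (312 + 36)/520 = 66.9% and the gap is 3.8 points, not 1.9. In the Step 3 model (s = 0.5, r = 0.8, equal true sensitivities), Pap's spurious lead is 5.6 points over an independent test but 1.1 points over one with 10% total discordance.
- *Pap cut-off below HSIL.* If 30% of cases have HSIL cytology and 30% lower-grade abnormality, inflation at r = 0.8 is (0.30 + 0.24)/0.86 − 0.60 = 2.8 points; at r = 0.9 it is 1.3.
- *Lesions arising by 18 months.* If they make up 10% of counted cases and the baseline Pap was positive in 10 to 30% of them, a sensitivity of 50% becomes 0.45 + 0.01 = 46% to 0.45 + 0.03 = 48%.

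**The case against.** The strongest reply is that cytology does not act alone, and this stands. Colposcopy decides jointly, minor positive colposcopies are biopsied in both groups, high-grade lesions once identified are treated whatever the Pap, and major colposcopy with low histology reaches an MDT in both groups. A reader might infer that cytology by itself decides who has excisional histology; the documents do not say that.

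A reader might also infer that Pap sensitivity is inflated against every other test. That does not follow. LBC is prepared from the vial in which the Pap brush was washed, and dual staining is also read on cells, so both may share the gain. Untreated women are retested at 18 months and lesions found then count as outcomes, which moves r towards 1, while newly arisen lesions can lower Pap sensitivity. The net direction is probable, not proven.

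Two of the statements have milder readings. The abstract sentence can fairly be taken to mean the additional specimens, since the same paragraph says that screening includes Pap. The Discussion sentence concerns the lack of colposcopy in HPV-negative women, and all HPV-positive women are indeed referred. Its closing words still exclude verification bias from triage altogether.

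None of this makes cytology's evaluation unbiased. Blinded histology review protects the reading of slides, not who yields tissue. The 18-month round depends on attendance, starts with an HPV test, and takes biopsies only if colposcopy is positive. The sensitivity analyses named in the article cover non-attendance and inadequate results. A fuller analysis may sit in a document not shown, so its absence is not the finding. The finding is that the article claims a property the design lacks for one candidate.

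**Conclusion.** The point holds in a limited form. The unqualified claim in the strengths box, and the Discussion's exclusion of triage from verification bias, are not supported for cytology. Comparisons of Pap with triage tests not strongly correlated with it are open to differential verification bias, probably favouring Pap.

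The documents do not establish its size. Under the assumptions shown it runs from about 1 point (r = 0.95) to more than the 5-point design difference (r below about 0.82), and it is smaller with a lower Pap cut-off or a correlated comparator. Comparisons among tests that do not involve cytology are not the target of this point, although tests correlated with cytology could share part of the effect.

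**What to change.** Leave clinical management as it is.

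1. **Wording.** Qualify the strengths box and the Discussion so that the unbiased claim excludes cytology. Clarify in the abstract that the sentence on management refers to the additional specimens, not the enrolment Pap.

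2. **Sensitivity analysis for every comparison involving cytology.** Do not count HSIL+ as a confirmed case when it was found only at an excision that the pathway for cytology below HSIL would not have triggered:
   - after a negative colposcopy;
   - after biopsy below CIN2 without a major colposcopy;
   - after TZ3 with an endocervical sample below HSIL.

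   Treat these women's status under a common work-up as unknown. Report bounds (all diseased, all not diseased) or imputation beside the primary estimate, for specificity and predictive values as well. In the k = 20 illustration the Pap sensitivity bounds would be 308/500 = 61.6% and 288/480 = 60.0%.

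3. **Keep cases from direct LLETZ after a major colposcopy.** These women may have no biopsy, but most of their disease would be found under either pathway. Dropping them would create a larger bias the other way: if 100 of the 480 were such cases, Pap would fall to 188/380 = 49.5% and the gap to a 65% comparator would become 15.5 points. Keeping them may leave a small residual advantage for Pap, which should be stated.

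The study forms already record colposcopic impression, biopsy details and the reason for LLETZ. It should be checked that the reason categories, read with the colposcopy and histology results, identify the three groups. The cost is some wording and one extra analysis with somewhat fewer confirmed cases.

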**Figure 2 F2:**
[figure not shown]
Clinical management of women in the study cohort. CIN, cervical intraepithelial neoplasia; HPV, human papillomavirus; HSIL, high-grade squamous intraepithelial lesion; LLETZ, large loop excision of the transformation zone; MDT, multidisciplinary team.

##### Women with cytology HSIL or more severe lesion (HSIL+)

Treatment with LLETZ should be offered without prior histology confirmation to women with a ‘positive major’ colposcopy, whenever possible. Biopsies should be collected if the colposcopy is considered ‘positive minor’ or where LLETZ without confirmed CIN2 is not allowed. If a transformation zone type 3 (TZ3) is observed, an endocervical sample should be collected and an excision type 3 (LLETZ to excise lesions which endocervical extent is not visible) diagnostic or therapeutic should be performed.

The clinical management of women with discordant results: lesions less than CIN2 (<CIN2) or those with negative colposcopy but with HSIL+ cytology should be revised at multidisciplinary team (MDTs) meetings, that are attended by the cytologist, pathologist, colposcopist and the local principal investigator at least. During the MDT, cytology, histology and colposcopy results, considering the age and parity of the woman, should be discussed to finally recommend treatment or recall for a second HPV test 18 months later. In the benefit of women, who may be lost to follow-up, recommendation for LLETZ will be prioritised above 18 months recall.

##### Women with cytology less than HSIL (<HSIL), unsatisfactory or unknown cytology

Biopsies should be collected from all women with positive colposcopy. An endocervical sample should be collected from women with TZ3 and if the result of this sample is HSIL+, treatment (excision type 2 or 3) should be offered. Women with histology <CIN2, negative colposcopy and those with a TZ3 and <HSIL on the endocervical sample should be recalled at 18 months. MDTs should be carried out when the colposcopy is positive major but the histology is <CIN2.

The colposcopic impression using a standard colposcopy nomenclature and specific colposcopy features (eg, size and location of observed lesions, number and severity of biopsies collected) are recorded in colposcopy study forms.

At the treatment visit, first a colposcopy is done followed by LLETZ. The reason and type of LLETZ as well as the colposcopic impression are recorded in treatment study forms. A pregnancy test is administered to participants before treatment with LLETZ and local consent forms for surgical procedures are sought. Self-reported adverse events are documented.

#### Visit 3: follow-up HPV test at 18 months

All women who were not treated after an initial positive screen are invited to a final follow-up screening with HPV testing 18 months after enrolment. Women will be allowed to attend this visit up to 30 months after enrolment or until the study ends. To increase attendance to this visit, women may self-collect a vaginal sample either at the health centre or at home (depending on the follow-up strategy). If this was the case, women will be explained what self-sampling is and how to self-collect a sample using a graphical brochure. Women will be given either a *care*Brush (QIAGEN) to be inserted in a specimen transport medium to be tested with hybridisation techniques or a swab to be inserted into a tube with no preservation medium to be washed in PC and tested with PCR techniques. Alternatively, a clinician will perform a pelvic exam and collect the sample using a cytobrush to be washed in a PC vial. The clinician-collected sample will be used for HPV testing and future triage tests. HPV-negative women exit the study and return to local regular screening. HPV-positive women will be referred for a final colposcopy round for diagnosis and treatment.

#### Visit 4: final colposcopy

The clinical management of women attending final colposcopy will be defined only by the colposcopic impression. Biopsies will be collected if the colposcopy is positive and an endocervical sample will be collected if a TZ3 is observed. Women with local CIN2+ histology will be treated with LLETZ and those with HSIL+ endocervical cytology will be treated with excision type 3; afterwards these women exit the study and return to routine healthcare. Women with histology <CIN2 or endocervical cytology <HSIL or negative colposcopy also exit the study and return to routine healthcare.

All women exiting the study are given a report with their screening and diagnosis results and clear indications on how to continue with routine follow-up care. Study colposcopists who usually work on a hospital that covers the area selected for ESTAMPA (EStudio multicéntrico de TAMizaje y triaje de cáncer de cuello uterino con pruebas del virus del PApiloma humano; Spanish acronym), have committed to follow-up treated women. It has been agreed that follow-up may be done by HPV testing or Pap with colposcopy of those HPV-positive or with abnormal smears, and that the first follow-up visit should be done at 6 or 12 months in accordance with local regular care.

